#### Analysis plan

The primary objective is to determine whether POPS + IYS is more effective, compared to POPS alone or Usual HS Exposure, in reducing adiposity measures (BMI z-score, skinfolds thickness). Additional focal outcomes are dietary intake, TV viewing, ATDG, emotional eating, and food-related tantrums. Baseline comparability of the 3 groups will be assessed. To account for clustering of children within a classroom, Proc Mixed in SAS with a random intercept for classroom will be used to analyze continuous outcomes, and General Estimating Equations (GEE) techniques [90] will be used to compare the prevalence of obesity and overweight across the 3 groups. Analyses will be conducted both with and without adjustment for baseline characteristics such as age, sex, race, and baseline BMI or BMI z-score. All models will incorporate covariates that are related to the outcomes to reduce residual variance and thus help reduce Type II error. Significance will be assessed using a two-sided test at α = 0.05.

Analyses will be based on the intention to treat principle where all randomized participants, including dropouts, are included in the analysis based on their randomized intervention group [90]. Given that a substantial portion of participants will likely have only partial adherence to the intervention (e.g., only attend some parent sessions), dose–response analyses will also be performed where dose corresponds to number of sessions attended.

As outlined in the conceptual model (Figure 1), analyses will be conducted to test whether the effect of POPS + IYS on obesity-related health behaviors and adiposity indices is mediated by self-regulation (using parent-reported, teacher-reported, and direct child assessment measures). As a secondary analysis, models will also be examined separately for boys and girls, white and non-white children, and children who are overweight or obese versus non-overweight at baseline.

Finally, process data on recruitment, retention, participant engagement in the intervention, participant and educator satisfaction, and implementation fidelity will be analyzed using descriptive and qualitative approaches, to inform continued collaborations with HS and allow more effective dissemination of findings.

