## Methods/design

### Study design

The Growing Healthy study is a randomized controlled trial (RCT). Classrooms (*n* = 75) are randomized through an automated system to one of 3 study arms (200 children per arm): (1) POPS; (2) POPS + IYS; or (3) Usual HS Exposure. Each HS program hosts all 3 study arms, and all children in an individual classroom participate in only one arm. Only one classroom participates per physical school site to prevent cross-contamination across study arms and ensure that participants are blind to group assignments. Families are assigned to study arm as a function of their classroom assignment. Every effort is made to match intervention and comparison classrooms on demographic characteristics in order to minimize differences not due to the intervention (e.g., % minority race/ethnicity, teacher education).

Data are collected pre-intervention (in the fall) and post-intervention (in the spring). Interventions occur between October and April of the academic year. Process implementation data are collected throughout the study. Children are enrolled in each of 4 academic years, with 50 children enrolled into each of the 3 study arms per year. Data collectors are separate from the interventionists, and blinded to the study arm to which participants in a classroom are assigned.

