### Participants and recruitment

Participants are from three HS programs in mixed rural and urban areas of Michigan. These programs serve 3,222 children (67% white, 28% black; ethnicity 23% Hispanic; 12.6% English as second language) per year in 184 half-day classrooms. The prevalence of overweight (BMI ≥ 85th percentile and < 95th, based on US Centers for Disease Control (CDC) reference growth curves for age and sex), 16.2%) and obesity (BMI ≥ 95th percentile, 17.0%) in these programs is similar to other HS cohorts [3,58]. Inclusion criteria are that the child is aged 3 or 4 years at study enrollment. Exclusions are significant developmental disabilities that would preclude participation, child is a foster child, or parent is non-English-speaking. Almost all families in the participating HS programs have annual household incomes below the federal poverty line, as this is an eligibility requirement for 90% of the children enrolled.

Families are told about the study during classroom open houses and through flyers in children’s backpacks, and compensated for returning an initial enrollment packet, including a signed written informed consent form. They are then contacted by telephone to review eligibility criteria that they reported in the enrollment packet and to confirm complete understanding of the study and validate informed consent. Next, a data collector (blind to study condition) completes pretest assessments. Appropriate compensation, tokens of appreciation and regular contact from project staff are incorporated to enhance retention.

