**IYS-Teacher (Classroom Management)**	
**1**	The Importance of Teacher Attention, Encouragement, Praise
**2**	Motivating Children Through Incentives
**3**	Preventing Behavior Problems—the Proactive Teacher
**4**	Decreasing Students’ Inappropriate Behaviors
**5**	Building Positive Relationships With Students, Problem Solving

The IYS-Parent component (12–14 weeks, 2 hours/week) focuses on parenting skills such as using effective praise, incentives, limit-setting, and handling misbehavior. Concepts are discussed using video vignettes about parenting challenges. Parents complete homework and receive follow-up phone calls. IYS-Parent sessions are delivered by master’s-level mental health specialists (MHS) (one per HS program, employed by HS).

For the IYS-Child component, sixty 15–20 minute lessons are delivered throughout the year during "Circle Time" in HS classrooms, followed by small group activities. Lessons address self-regulation skills, problem-solving strategies, and prosocial behavior, and use child-size puppets to teach skills and engage children. IYS-Child lessons are delivered by the MHS, and HS teachers direct small group activities after each lesson. Teachers are mentored by MHS in delivering IYS-Child, so that delivery can slowly progress from delivery by MHS, to co-delivery by MHS and teacher, to sole delivery by the teacher over time, which is an effective model for dissemination [62]. MHS and teachers also receive training in classroom management strategies (e.g., handling transitions effectively), which is the IYS-Classroom component.

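### Head Start program and academic year structure the design but are not named as model terms, so the analysis may give away some precision

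*Protocol article*

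**What the plan says.** On the design, the protocol article's Participants and recruitment section says "Participants are from three HS programs in mixed rural and urban areas of Michigan". The Study design section adds that "Each HS program hosts all 3 study arms" and that recruitment runs over four academic years, "with 50 children enrolled into each of the 3 study arms per year". The randomized unit is the classroom, 75 in all.

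On the analysis, the Analysis plan says "Proc Mixed in SAS with a random intercept for classroom will be used to analyze continuous outcomes", with GEE for the prevalence of obesity and overweight. Results are to be produced with and without adjustment for baseline characteristics; the examples given are age, sex, race and baseline BMI or BMI z-score. A further sentence has every model take in covariates associated with the outcome, to cut residual variance. Program and academic year are not mentioned there, either as required terms or as excluded ones.

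**The concern.** When arms are spread evenly over a factor, differences between the levels of that factor cancel out of the arm comparison. They do not cancel out of the estimated classroom variance unless the model contains the factor. An analysis that omits it therefore reports a standard error larger than the true sampling variability of the arm contrast: intervals are too wide, the actual type I error is below the nominal .05, and power is lost.

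Here the candidate factors are three programs in mixed rural and urban areas and four successive years. Either could plausibly be related to diet, screen time or adiposity. The planned analysis without adjustment would, as written, leave both out. In the adjusted analyses their inclusion depends on whether they are judged to be associated with each outcome, which is not the same as a pre-specified term.

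**Working it through.** **Inputs from the protocol article.** 75 classrooms in 3 arms (25 per arm if equal); 150 children per arm after attrition, so m = 450/75 = 6 per classroom; intraclass correlations (ICC) of .05 and .20 from the power section; two-sided α of .05.

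**Input assumed.** s is the share of between-classroom variance that program and year terms would remove. The article gives no figure, so 0, .10, .25 and .50 are shown.

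**The plan's own figures.** The power section gives detectable effects of f = .16 at ICC .05 and f = .185 at ICC .20, with 80% power. A three-group F test with design effect 1 + (6 − 1) × ICC (1.25 and 2.00, so effective n per arm 150/1.25 = 120 and 150/2.00 = 75) gives f = .164 and f = .208. Power at the stated effects is 77.7% and 69.4%. The stated figures fit about 4 children per classroom (f = .158 and .186). That mismatch is a separate matter. The comparison below does not use f; it takes only the two ICCs and m = 6.

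**Formula.** With total variance set to 1, the variance of a classroom mean is

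- without program and year: V0 = ICC + (1 − ICC)/6
- with them: V1 = ICC(1 − s) + (1 − ICC)/6

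The SE ratio is √(V0/V1). If the arms are balanced over the factors, V1 governs the true variability of the contrast. The omitting model's actual type I error is then 2[1 − Φ(1.96 × ratio)].

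| ICC | s | V0 | V1 | SE ratio | Actual type I error without the terms |
|---|---|---|---|---|---|
| .05 | 0 | .2083 | .2083 | 1.000 | .050 |
| .05 | .10 | .2083 | .2033 | 1.012 | .047 |
| .05 | .25 | .2083 | .1958 | 1.031 | .043 |
| .05 | .50 | .2083 | .1833 | 1.066 | .037 |
| .20 | 0 | .3333 | .3333 | 1.000 | .050 |
| .20 | .10 | .3333 | .3133 | 1.031 | .043 |
| .20 | .25 | .3333 | .2833 | 1.085 | .034 |
| .20 | .50 | .3333 | .2333 | 1.195 | .019 |

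**Power.** Take an effect that would have 80% power if s were 0. Without and with the terms, power is:

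- ICC .05, s = .25: 80.7% and 82.4%
- ICC .05, s = .50: 81.5% and 84.8%
- ICC .20, s = .25: 81.9% and 86.0%
- ICC .20, s = .50: 84.3% and 91.8%

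**Simulation check.** There were 20,000 runs with 12 program-by-year strata, 2 classrooms per arm in each, and t tests on classroom means. At ICC .20 and s = .50, type I error was .021 without strata and .050 with them; power was 83% and 91%. At s = 0 the two analyses did not differ. The simulation fitted all 12 cells (11 degrees of freedom), more than the 2 + 3 = 5 needed for main effects. It also assumed perfect balance within cells, which the article does not state.

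All these figures are for continuous outcomes; none has been computed for the GEE models.

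**The case against.** The strongest reply is that the plan already provides for this. Its rule on covariates applies to all models and its list of examples is open. If program or year predicts an outcome, which is the only case where omission costs anything, the rule lets it in. A reader might infer that the models contain nothing but a classroom intercept; the Analysis plan does not support that. A journal article may also leave the exact list of terms to an SAP. This narrows the point but does not remove it. The article states its model and its example covariates without the factors its own design section relies on, the rule does not guarantee their entry, and the run without adjustment would leave them out.

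A second reply is that balance is only partly documented. Every program hosts all arms and each arm recruits equally each year. Equal arm numbers within each program, or within each program-by-year cell, are not stated, and nor is stratified randomization. A reader might infer full balance within cells; the article does not say so. The inflation therefore applies only as far as balance was achieved. This stands.

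Third, the size depends on an assumed share and may be nil. Baseline BMI z-score would already absorb part of any stable program or year difference in adiposity. This also stands, though that covariate is likely to do less for diet, screen time, delay of gratification or tantrums.

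Three further inferences are tempting and should not be drawn:

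- **Matching.** The statement that "Every effort is made to match intervention and comparison classrooms on demographic characteristics" does not call for matching terms in the model, because no pairs or blocks are defined.
- **Allocation.** The same statement does not show that classrooms were reassigned by hand. The article describes an automated draw, and matching could have come before it.
- **Specialists.** Having one mental health specialist per program for IYS-Parent is an arm-by-program matter, which a program main effect would not model.

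**Conclusion.** The point holds as a modest question of efficiency. The design spreads the arms over program and year, and the stated model names neither. If they predict the outcome, models without them give standard errors that are too large and conservative tests.

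With 6 children per classroom and arms balanced over these factors, the inflation is 0% if they carry no between-classroom variance. If they carry 10–50% of it, the inflation is about 1–7% at ICC .05 and 3–20% at ICC .20. The upper end needs the larger ICC and the largest assumed share together. At ICC .05 the power difference is about 2 to 3 percentage points for shares of 25–50%.

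A reader might take this as a threat to validity. It is not one: the arithmetic shows no bias in the arm effect and no excess of false positives.

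**What to change.** In the Analysis plan, name Head Start program (3 levels) and academic year (4 levels) as fixed effects in every Proc Mixed and GEE model. State that they stay in the analyses otherwise described as unadjusted, so that those omit child-level covariates but keep the design factors. Their inclusion should not depend on an observed association with the outcome.

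The cost is 2 + 3 = 5 of about 75 − 3 = 72 classroom-level degrees of freedom, leaving 67, plus one sentence of text. No new data are needed. If program and year turn out not to matter, almost nothing is lost.

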### Primary outcome measures

#### Anthropometry

Individuals are weighed without shoes or heavy clothing using a Detecto Portable Scale Model #DR550C and measured using a Seca 213/217 portable stadiometer. Duplicate measures are taken for both weight and height. Body mass index (BMI) is calculated and child BMI z-score derived (using CDC reference growth curves for age and sex [63]), in order to estimate prevalence of child obesity and overweight (classified per national recommendations [12]). Maternal weight and height are measured using the same methods, and maternal BMI calculated (kg/m^2^) for use as a covariate.

Triceps and subscapular skinfolds improve prediction of body fatness and correlate with chronic disease risk in children [64,65]. Duplicate measures of each skinfold in children are obtained using Lange Calipers (triplicates when tolerance of 2 mm is exceeded) [15,64].

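### Overweight, as the protocol defines it, is a middle BMI band with no fixed good direction and low sensitivity; the categorical comparison should use nested cut-offs

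*Protocol article*

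**What the plan says.** Three parts of the protocol article bear on this.

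- **Participants and recruitment** gives the only explicit cut points: "The prevalence of overweight (BMI ≥ 85th percentile and < 95th", with a prevalence of 16.2%, and "obesity (BMI ≥ 95th percentile, 17.0"%. The two categories are mutually exclusive. They are given as a description of the participating Head Start programs.
- **Anthropometry**, under Primary outcome measures, says that child BMI z-score is derived "in order to estimate prevalence of child obesity and overweight". It refers to national recommendations for the classification and does not restate cut points.
- **Analysis plan** states the primary objective on continuous measures, "in reducing adiposity measures (BMI z-score, skinfolds thickness". It then says that GEE "will be used to compare the prevalence of obesity and overweight across the 3 groups". It does not say whether overweight there means the band, everything at or above the 85th percentile, or one level of an ordered outcome. The same section does use a grouping that pools overweight with obese children, but only to form baseline subgroups.

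**The concern.** A category bounded on both sides gains children from above when they improve and from below when they worsen. Its prevalence therefore has no fixed good direction. A difference between arms in the band alone cannot be read as benefit or harm without knowing which boundary the children crossed.

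There is a second problem even when no reversal occurs. If the whole BMI distribution shifts down, children who enter the band from the obese range partly replace those who leave it at the bottom. The net change is then much smaller than the change at either cut-off. At stake is a supporting result on overweight that is hard to interpret or falsely reassuringly null, in a trial whose subject is obesity prevention.

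**Working it through.** The article gives no computed figure for this comparison, so there is none to reproduce. The check works out what the comparison would show.

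**Inputs from the article.** Overweight band 16.2% and obesity 17.0% (Participants and recruitment), so 16.2 + 17.0 = 33.2% at or above the 85th percentile. There are 75 classrooms and 3 arms (Study design), 150 analysed children per arm and an intraclass correlation of .05 (Sample size and power calculations). The test is two-sided at 0.05 (Analysis plan).

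**Assumptions.** The amount of movement is not in the article and is shown as a range. The correlation of .05 is carried over to the binary outcomes.

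**1. Movement across one boundary only.**
- 20% of obese children move into the band: 0.20 × 17.0 = 3.4 points. Obesity goes from 17.0% to 13.6%, the band from 16.2% to 19.6%, and the share at or above the 85th percentile stays at 33.2%.
- 20% of overweight children become obese: 0.20 × 16.2 = 3.2 points. The band falls from 16.2% to 13.0% and obesity rises from 17.0% to 20.2%.

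The band rises in the first case, which is improvement, and falls in the second, which is worsening.

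**2. Uniform downward shift.** Take BMI z as normal, with cut points set to the stated prevalences: 0.434 for 33.2% and 0.954 for 17.0%. For a downward shift s, obesity = 1 − Φ(0.954 + s), the 85th-percentile share = 1 − Φ(0.434 + s), and the band is the second minus the first.

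| Shift (SD) | Obesity | Band | At or above 85th |
|---|---|---|---|
| 0 | 17.0% | 16.2% | 33.2% |
| 0.1 | 14.6% | 15.1% | 29.7% |
| 0.2 | 12.4% | 13.9% | 26.3% |
| 0.3 | 10.5% | 12.7% | 23.1% |
| 0.4 | 8.8% | 11.4% | 20.2% |

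At 0.2 SD the band falls by 2.3 points and the cumulative share by 6.9 points.

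**3. Power.** Analysed children per classroom: 450/75 = 6. Design effect: 1 + (6 − 1) × .05 = 1.25. Effective children per arm: 150/1.25 = 120.

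For two arms, power = Φ[(|p1 − p2| − 1.96 × SE0)/SE1], where SE0 = √(p̄(1 − p̄) × 2/120), p̄ is the mean of p1 and p2, and SE1 = √([p1(1 − p1) + p2(1 − p2)]/120). For a 0.4 SD shift:
- Band, 16.2% v 11.4%: (0.0478 − 0.0873)/0.0444 = −0.89, power about 19%.
- Obesity, 17.0% v 8.8%: (0.0822 − 0.0848)/0.0429 = −0.06, power about 48%.
- At or above 85th, 33.2% v 20.2%: (0.1300 − 0.1119)/0.0565 = 0.32, power about 63%.

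At 0.3 SD the band has about 12% and the cumulative cut about 41%.

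**4. How often a reversal would be significant.** In the first example of step 1 (16.2% v 19.6%, 120 effective children per arm), the chance of a significant rise in the band is about 10 to 11%.

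**The case against.** The strongest reply is that the article never fixes the band as a tested outcome. The cut points describe the source population, the outcome classification is left to a cited recommendation that is not at hand, and the Analysis plan sentence can be read as a combined or ordered outcome. The pooled baseline subgroup shows that the authors also think in terms of the 85th-percentile cut. How a category is coded is often left to a fuller document.

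Part of this stands. The sentence does not exclude a cumulative or ordinal reading, and the point must be put conditionally. But the article does define overweight, does report it beside obesity as a separate prevalence, and does name the comparison. Its one definition leads to the band. The problem comes from joining two things that are stated, not from a missing detail.

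A reader might also infer that an arm which moves obese children down will score worse in this trial, or that a harmed arm will look better. The documents do not support that.
- It would apply to the overweight comparison only. The same movement improves obesity prevalence and the primary BMI z-score.
- It needs entries across the 95th percentile to outnumber exits at the 85th. Under a uniform shift the band moves the right way: down with benefit, and up to 18.2% and 19.7% for upward shifts of 0.2 and 0.4 SD.
- Nothing in the article suggests movement across one boundary alone within an academic year.

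**Conclusion.** The point holds in a limited form. Read with the only definition in the article, the GEE comparison of overweight tests a middle band whose rise or fall has no fixed meaning. Under a uniform downward shift the likely damage is a muted effect rather than a reversed one, with about a third of the change seen at the 85th-percentile cut at 0.2 SD (2.3/6.9) and power of about 19% against 63% at 0.4 SD.

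These figures rest on a normal BMI z, a uniform shift of assumed size, the program-wide prevalences and six analysed children per classroom. The muting itself follows from having two boundaries and does not depend on an unusual pattern of movement.

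The primary conclusions are not at risk: the continuous BMI z-score and skinfold analyses and the obesity comparison are untouched. This is a worthwhile correction to a supporting analysis.

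**What to change.** In Anthropometry and in the Analysis plan, state the binary GEE outcomes as nested cut-offs: BMI at or above the 95th percentile (obesity) and BMI at or above the 85th percentile (overweight or obese). Report the 85th-to-below-95th band descriptively only. Movement from obese to overweight then lowers the first outcome and leaves the second unchanged. For example, a move of 4 points gives obesity 17.0% to 13.0% with the combined share still 33.2%, so neither outcome worsens.

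The cost is about one sentence in each section, with the same data and the same GEE approach. The two outcomes overlap, so their results should not be read as independent evidence. An ordinal GEE on the three ordered categories is an alternative, but it adds a proportional-odds assumption that would need to be stated and checked.

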### Sample size, power calculations, and data analysis

#### Sample size and power calculations

Enrolling 200 participants per arm, assuming attrition of 25%, will achieve a final sample size of 150 participants per arm. This sample size of 150 per arm will enable detection of small to moderate effect sizes of f = .16 (between groups vs. within group variation), with a power of 80%, α = .05 and assuming and intraclass correlation *r* = .05. This sample size also provides 80% power with *r* = .20, α = .05 to detect an effect size of f = .185.

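### The only subgroup method the article states is separate models within sex, race and baseline-weight strata, which do not test whether the intervention effect differs between strata

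*Protocol article*

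**What the plan says.** The Analysis plan section of the protocol article describes the subgroup work in one sentence. It is introduced by "As a secondary analysis" and continues: "models will also be examined separately for boys and girls, white and non-white children". The third factor is "children who are overweight or obese versus non-overweight at baseline". That makes three factors and six strata.

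The only decision rule in the section is general: "Significance will be assessed using a two-sided test at α = 0.05". No arm-by-subgroup term is named, and nothing says how the results of two strata will be compared. For the main analysis the same section specifies Proc Mixed with a random intercept for classroom, and GEE for prevalence of overweight and obesity.

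**The concern.** Models are fitted by sex, race or baseline weight to learn whether the programs work differently in those groups. Separate fits do not answer that. Each compares its own effect with zero, using fewer children than the whole trial. When one stratum passes the 5% threshold and the other does not, the two effects may still be identical.

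The stated method therefore yields side-by-side p-values that invite a comparison they cannot support. At stake is a report that a program works in one sex, one racial group or one weight group when the data show no such difference. The primary comparison of arms is not affected.

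**Working it through.** **Inputs**
- Sample size section: "Enrolling 200 participants per arm, assuming attrition of 25%, will achieve a final sample size of 150 participants per arm". This reproduces: 150 / (1 − .25) = 200.
- Sample size section: 80% power at f = .16 with intraclass correlation (ICC) .05, and at f = .185 with ICC .20, α = .05.
- Study design section: 75 classrooms in three arms, so 25 per arm and 450/75 = 6 analysed children per classroom.
- Participants section (program figures, assumed to hold in the trial): 67% white; 16.2% + 17.0% = 33.2% overweight or obese. Both are close to a 67/33 split.
- Sex split 50/50: my assumption, as the article gives none.

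**The plan's power figures.** A three-group F test with 6 children per classroom gives .76–.78 at f = .16, ICC .05, and .68–.70 at f = .185, ICC .20. Four per classroom, which the article does not state, would give about .81 and .80. This is a separate matter. Below I take the planned 80% for one two-arm contrast, so the noncentrality is 1.96 + .84 = 2.80. The simulation further down does not use that shortcut.

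**Step 1: strata treated as independent.** Equal halves: power Φ(2.80 × √.5 − 1.96) = .508 in each, so P(exactly one significant) = 2 × .508 × .492 = .50. For 67/33 the powers are .63 and .36, and P(exactly one) = .63 × .64 + .36 × .37 = .54.

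**Step 2: allow for shared classrooms.** Both strata sit in the same classrooms, and arms are assigned by classroom, so stratum estimates are positively correlated. With m children of a stratum per classroom, the variance is proportional to v(m) = ICC + (1 − ICC)/m. The stratum noncentrality is 2.80 × √(v(6)/v(m)), and the correlation between strata is ICC/√(v(m1)·v(m2)).

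Example, ICC .05, split 3/3:
- v(6) = .05 + .95/6 = .2083 and v(3) = .05 + .95/3 = .3667, ratio .568.
- Noncentrality 2.80 × √.568 = 2.11, power Φ(2.11 − 1.96) = .56.
- Correlation .05/.3667 = .136. The bivariate normal gives P(both) = .335.
- P(exactly one) = 2 × (.56 − .335) = .45.

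| ICC | Children per classroom | Stratum power | Correlation | P(exactly one) |
|---|---|---|---|---|
| .05 | 3 / 3 | .56, .56 | .14 | .45 |
| .05 | 4 / 2 | .66, .42 | .13 | .49 |
| .20 | 3 / 3 | .66, .66 | .43 | .33 |
| .20 | 4 / 2 | .72, .55 | .41 | .37 |

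**Step 3: simulation.** 4,000 trials per setting, 25 classrooms per arm, 6 children each, random classroom intercept with known variance components, same true effect in both strata. Results per factor:
- f = .16, ICC .05: .44–.50 (at least one of three factors: .74–.75).
- f = .185, ICC .20: .36–.42 (at least one of three: .64–.66).

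**Step 4: other effect sizes.**
- Half the design effect: .26–.28 by the step 2 formula; .24–.31 simulated at f = .08, ICC .05.
- No effect: .085–.094 by the formula, slightly lower in simulation.
- A larger effect, f = .25, ICC .05: .11–.29 simulated.

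**Step 5: the alternative.** An interaction test is wrong at its nominal 5% per factor whatever the common effect, or 1 − .95³ = 14% for at least one of three independent factors.

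**Power of the interaction test.** The classroom intercept cancels, so the variance is proportional to (1 − ICC)(1/m1 + 1/m2). At ICC .05 and 3/3 this is .95 × 2/3 = .633, which is 3.04 times v(6). If the strata differ by as much as the whole planned effect, the noncentrality is 2.80/√3.04 = 1.61 and power is .36. For 4/2 it is .33. At ICC .20 the figures are .60 and .55.

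**The case against.** Four points can be made for the plan.

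- **The article does not say that effect modification will be judged by significance in one stratum and not in the other.** A reader might infer it, but the text says only that models will be examined by stratum, as a secondary analysis. This stands, and the point should not be put that way.
- **An interaction test may be in the statistical analysis plan, which is not at hand.** If the article were merely silent on subgroup method, that would settle it. But it does state a method, and that method is stratification. A further test elsewhere would supplement what is stated here.
- **The word models follows a sentence on mediation and might refer to mediation models.** The ambiguity is real. It does not rescue the method, since separate mediation fits do not test a difference between strata either.
- **The size is easily overstated.** A reader might infer that spurious one-group-only results arise about half the time in general. That needs a common true effect near the design size. The plain .50 and .54 also ignore shared classrooms, which lower the figure, most clearly at ICC .20. This stands, and steps 2 to 4 allow for it.

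Two further inferences lack support. Nothing in the article ties dissemination through Head Start to subgroup results, so harm by that route is speculative. And small numbers of children per classroom within strata have not been shown to bias the separate fits.

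**Conclusion.** The concern holds in limited form. Separate models in six strata, each tested at 5%, cannot show whether the intervention effect differs by sex, race or baseline weight, and no other subgroup method is stated.

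With the same true effect in both strata and near the planned size, a significant/non-significant split would occur in roughly 45–50% of trials per factor at ICC .05 and about 33–42% at ICC .20. It falls to about a quarter to 30% at half that effect and about 5–10% with no effect. The comparator is a nominal 5% for an interaction test at any common effect size.

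These figures rest on 6 analysed children per classroom, program-level race and weight splits, an assumed even sex split, and a random classroom intercept only. They describe what the stated method would produce if splits were read as differences, which the article does not commit to. The analysis is secondary, so this is a worthwhile correction and not a threat to the main result.

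**What to change.** Replace the separate models with arm-by-subgroup interaction terms in the full-sample model already planned: Proc Mixed with the classroom random intercept for continuous outcomes, GEE for prevalence. With three arms this is a 2-df test per factor, or 1 df for each prespecified contrast. Report stratum estimates with confidence intervals from that same model. Base any statement of a differential effect on the interaction test for the adiposity outcomes (BMI z-score and skinfolds), and label it secondary. The subgroups are already fixed by baseline status or do not change, so their definitions need no revision.

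The cost is a few model terms, with no extra data or enrolment. The drawback is low power, which the plan should state: about one in three at ICC .05 even for a difference between strata as large as the whole planned effect. A non-significant interaction is then not evidence that the effects are equal.
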